### 2.3. Inclusion Criteria

Diagnosis of PCOS according to the Rotterdam criteria (Revised 2003 Consensus on Diagnostic Criteria and Long-Term Health Risks Related to Polycystic Ovary Syndrome, 2004). Hyperandrogenism will be evaluated through hirsutism, alopecia, acne, or through the calculation of total free androgen when clinical signs are not clear [48]. Hirsutism should be assessed using the modified Ferriman–Gallwey score (mFG), where a level ≥ 4 to 6 indicates hirsutism. Alopecia will be assessed using the Ludwig visual score. For acne, no universally accepted visual assessment is available. When clinical signs of hyperandrogenism are unclear or absent, measurement of calculated free testosterone, free androgen index, or calculated bioavailable testosterone should be undertaken [48]. Ovulatory dysfunction is clinically reflected by irregular menstrual cycles, which are defined as less than 21 or more than 35 days in women over 3 years postmenarche to perimenopause.

### 2.4. Exclusion Criteria

The exclusion criteria will be women diagnosed with congenital adrenal hyperplasia (CAH), androgen-secreting tumors, Cushing’s syndrome, thyroid dysfunction, and hyperprolactinemia; women below 18 y.o.; pregnancy within the past 6 weeks; within 6 weeks postabortion or postpartum; breastfeeding within the last 6 months; not willing to give written consent to the study; patients with a history of heart problems, stroke, seizures, or epilepsy.

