## 1. Introduction

Polycystic ovary/ovarian syndrome (PCOS) is considered the most frequent endocrine pathophysiology among women of fertile age, displaying a prevalence between 5 and 15% relative to the clinical diagnostic criteria [1]. Azziz et al., 2004, estimated an annual cost of about 4.37 billion dollars spent in identification and management of the PCOS condition in the USA, which demonstrates the importance of investing in solutions for this condition’s symptoms. With a still unidentified origin, the diagnostic of this syndrome is always made by exclusion of conditions that mimic the phenotypes [2]. In 2003, the European Society for Human Reproduction and Embryology (ESHRE) and the American Society for Reproductive Medicine (ASRM) reformulated the diagnosis criteria of PCOS. Two out of the following three criteria should be present to confirm the syndrome: oligo/anovulation, androgen excess, and the confirmation of polycystic ovarian morphology by imaging. These are designed as Rotterdam criteria, and from them, it is possible to identify four distinct phenotypes of PCOS (Table 1). PCOS has been strongly associated with alteration in the autonomic nervous system: namely, increased sympathetic nervous activity [3]. Endocrine and metabolic implications of the syndrome reflect a high comorbidity [4] within three major aspects: hyperandrogenism [5,6,7,8] and reproductive issues [9,10,11,12], metabolic [13,14,15,16,17,18], and mental or emotional [19,20,21,22,23,24,25,26]. Different clinical strategies have been designed for PCOS management according to international guidelines [11,27,28,29]. However, allopathic therapies have shown several unpleasant secondary effects, which motivate PCOS women to search for complementary medicines such as traditional Chinese medicine (TCM). Among the TCM therapeutics, acupuncture has been used as therapy or co-therapy to improve the comorbidity’s symptoms affecting women with this condition. Diverse studies using low frequency electroacupuncture (EA), alone [30,31] or in combination with exercise to modulate the sympathetic system, concluded that acupuncture seems to regulate the hypersecretion of androgens, improving both the reproductive and endocrine metabolic functional state [32]. Acupuncture has also been used, alone or in combination with clomiphene, to ameliorate the disorder of subfertility in PCOS patients [33,34]. With respect to psychological balance, acupuncture studies were designed to relieve anxiety and depression in PCOS patients [35]. Acupuncture therapy is thought to have a positive impact on the treatment of PCOS through the following mechanisms: sympathetic output modulation through spinal reflexes [36]; modulation of hypothalamic–pituitary–adrenal (HPA) and hypothalamic–pituitary–gonadal (HPG) axes through the increase of β-endorphin secretion [37,38,39,40,41,42]; and influencing insulin sensitivity or resistance through functional balance of the insulin signaling pathways [43]. PCOS in TCM is considered a complex combination of different factors that end up in blockage of the communication between the Penetrating (Chong Mai) and Conception (Ren Mai) vessels, compromising the female’s fertility and reproductive cycle normalization, with or without association to pathogenic heat and phlegm (Lyttleton, 2013). Usually, patients present a tendency to a kidney Yang and/or Yin deficiency, possibly associated to a Qi deficiency in spleen or lung, hence leading to a weakened Shen in the long run. On the other hand, we can have a scenario where kidney Yang deficiency may be associated to Xue stasis leading to cardiac phlegm/dampness in the long run, and, therefore, a disturbed Shen. Main pathogenic factors generating this condition may be stress/overworking, emotional origin (sadness, fear, or excessive worry), cold or phlegm/dampness. According to Maciocia, the kidney is the internal organ most closely associated to the ability to conceive, therefore kidney deficiency is the pattern most commonly found among gynecological pathologies. Kidney deficiency can be due to kidney Yin and/or kidney Yang deficiency. The same author referenced that the overlap of blood and kidney deficiency are quite common due to the relation of kidneys/uterus/blood/Penetrating vessel (Chong Mai). The Penetrating vessel supplies blood to the uterus; however, this supply is also managed by the provision of blood from the liver, the internal organ that stores the blood. So, this liver-blood is key for a healthy menstrual function. Not to mention that, according to the Five Element Theory, Water is the mother of Wood, meaning that the kidney organ is the mother of the liver which is consensual with the relation between essence and blood: kidneys store Jing/essence and the liver stores blood; hence, essence is the mother of the blood. Most published studies of acupuncture in PCOS are concerned with anovulatory cycles and sub/infertility, addressed in TCM as TianGui disorder [44], which is the disorder for which most women seek for help in complementary medicine. However, many women also search for the treatment of symptoms associated with hyperandrogenism either for aesthetic reason, such as acne and alopecia, or for derived comorbidities such as overweight, insulin resistance, diabetes type II, and others. Recent analysis of obstetric outcomes in TCM syndromes showed that possibly more than the usual two distinctions between kidney deficiency and phlegm-dampness and/or blood stasis may be found in women diagnosed with PCOS. Wang et al. (2017) made a secondary analysis of the results of the RCT of Wu et al., 2016, and concluded that it is possible to identify four TCM phenotypes that could be correlated with the four phenotypes according to the Rotterdam criteria (Table 1). According to the author, these four TCM phenotypes would be: “kidney deficiency and liver stasis” (40.29%), “spleen deficiency and phlegm stasis” (32.27%), “phlegm stasis and blood stasis” (16.55%), and “kidney deficiency and blood stasis” (10.89%)—to help in understanding the syndromes according to TCM, we can leave a quick definition of these patterns regarding the reproductive function. According to Lyttleton, kidney deficiency can be translated in symptoms such as in the study, where kidney deficiency with liver stasis patients showed a tendency to have psychological or mental problems [45]. Spleen deficiency and phlegm stasis patients presented metabolic abnormalities, including higher body weights, body mass index, waist and hip circumferences, systolic blood pressure, free androgen index, triglycerides, alanine transaminase, and occurrence of metabolism syndrome. Patients with phlegm and blood stasis had higher free testosterone and insulin, and patients with kidney deficiency with blood stasis presented a more severe reproductive disorder including higher luteinizing hormone and the ratio of luteinizing hormone to follicle stimulation hormone. In general, patterns derived from kidney deficiency demonstrated an association with psychological or mental problems, while patterns associated to phlegm syndrome had more severe glucolipid metabolic abnormalities.

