### 2.2. Recruitment, Participants, and Randomization

We propose a two-armed pilot study comparing the effects of active acupuncture (SG) with sham acupuncture (CG). The flow chart of the study design is shown in Figure 2. The sample will be 120 women, divided in two main groups according to the TCM diagnosis: Group A (*n* = 60): kidney deficiency associated with phlegm-dampness syndrome and/or spleen deficiency or liver stasis and group B (*n* = 60): kidney deficiency with main symptoms of blood stasis. Each group should have a total of 60 participants to achieve statistical difference in the case of 20% withdrawal of the participants [34]. Participants will be recruited directly from the family doctor and/or hospital specialty of gynecology/endocrinology. Each medical practitioner will refer patients with PCOS diagnostic aged between 18 and 59 y.o. with main symptoms of metabolic imbalance and women between 18 and 40 y.o. with main symptoms of hyperandrogenism and fertility issues to the principal investigator to be later recruited by telephone interview. Patients who show interest in participating will first be prescreened and recorded by an intake to verify that they meet basic inclusion criteria. All questions about the study, as well as the written informed consent, will be explained in detail. The goal of the screening visit will be to confirm a diagnosis of PCOS and to exclude major medical illnesses. These tests will aim to confirm the western and TCM diagnostic. Women diagnosed with kidney deficiency associated with phlegm-dampness will be randomly allocated by a computer program in a 1:1 ratio to two groups of 30 individuals each, one will be the study group (SGA) submitted to active acupuncture, and the other will be the control group submitted to sham acupuncture (CGA). The same procedure design will be applied to the 60 women diagnosed with kidney deficiency associated with blood stasis (SGB and CGB). All baseline and follow-up measures should be obtained on a single day. However, questionnaires may be spread between the screening and the baseline visit (Table 2).

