### 2.5. Intervention

A schedule was established for a total of 12 weeks of intervention, with a frequency of treatment of 1 time per week during the first 6 weeks and 2 times per month in the following 6 weeks. Treatments will take place at a research center/private TCM clinic (Figure 2 and Table 2).

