### 3.1. Blinded

A random code and blind code will be conducted by a “third party” independent of the study using opaque envelopes. The envelopes will be sealed and shuffled, and the assignment records will not be disclosed until the end of the study. Trial participants, formal physicians, therapists, outcome assessors, and data analysts will be blinded to the treatment allocation to minimize potential sources of bias. Only acupuncturists will not be blinded to the treatment allocation. Licensed acupuncturist profile with at least five years of experience will be recruited and will be trained to administer acupuncture. The techniques for the entire treatment procedure will be standardized between practitioners. Results will be kept sealed until the end of the intervention phase. Data analysis will be conducted independently by an experienced statistician, independent of the research team.

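### The exclusion list sets no limit on current or recent acupuncture, so women already receiving the treatment under test can be randomised

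*Protocol article*

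**What the plan says.** Section 2.4 of the protocol article sets out its list in full. It opens with "The exclusion criteria will be women diagnosed with congenital adrenal hyperplasia (CAH), androgen-secreting tumors, Cushing’s syndrome, thyroid dysfunction, and hyperprolactinemia", goes on to women under 18, and gives time limits for recent pregnancy, abortion or birth (6 weeks) and for breastfeeding (6 months). It closes with "not willing to give written consent to the study; patients with a history of heart problems, stroke, seizures, or epilepsy". Acupuncture is not mentioned.

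The neighbouring sections do not fill the gap. The inclusion criterion in 2.3 is "Diagnosis of PCOS according to the Rotterdam criteria", with detail on hyperandrogenism and cycle length. On screening, 2.2 says: "The goal of the screening visit will be to confirm a diagnosis of PCOS and to exclude major medical illnesses". That section also mentions an intake record but does not itemise it.

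On masking, section 3.1 states: "Trial participants, formal physicians, therapists, outcome assessors, and data analysts will be blinded to the treatment allocation". Only the acupuncturists know the arm.

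**The concern.** Section 2.4 sets time windows for other states that could disturb the hormonal outcomes, but none for the intervention being tested. That has two possible effects.

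- **Dilution.** A woman who is having acupuncture, or had it shortly before entry, may carry some of its effect into baseline. If that effect persists, further active sessions have less to add and a sham allocation does not take it away, so the observed contrast shrinks.
- **Blinding.** A woman who knows what needling feels like has a reference that a naive woman lacks, and may be better placed to recognise the sham. If so, her self-rated scores could move with her guess, and a woman who thinks she has sham could be more inclined to leave.

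The question is how far the article supports each effect, and whether either can be sized.

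**Working it through.** **1. Is the restriction absent?** Sections 2.2, 2.3 and 2.4, read together, contain no criterion on past, recent or current acupuncture and no washout. Table 2 lists an eligibility screen and baseline assessments without itemising them. The omission is therefore established for the stated eligibility rule. It is not established that prior exposure goes unrecorded.

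**2. Dilution.** Let Δ be the true active-sham contrast in women without recent acupuncture, p the share recently or currently treated, and h the fraction of the effect that those women already hold and keep through assessment, whichever arm they are in. Then

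observed contrast = (1 − p·h) × Δ.

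Randomisation makes p equal in the two arms in expectation, so the formula shrinks the contrast without favouring either arm. The documents give neither p nor h. For scale only: if p were 10% to 30% and h = 1, the contrast would be 0.90Δ to 0.70Δ. Since h = 1 means the full effect is already held and later sessions add nothing, this is the upper case for those values of p.

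**3. Blinding.** The arms differ visibly for every participant. Active treatment uses 14 needles (Protocol A) or 16 (Protocol B) on abdomen, limbs and head, rotated to evoke de Qi and stimulated again at 10, 20 and 30 minutes (2.5.1). Sham is superficial needling at the shoulders and upper arms with no stimulation (2.5.2). Naive women may guess too, so the eligibility rule is responsible only for the excess:

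attributable bias = share experienced × (guess-driven gap in experienced women − the same gap in naive women).

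None of these three quantities is in the documents.

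**4. Which outcomes are exposed?** SF-36 and the two Zung scales are self-rated, and section 3 and Table 3 class them as exploratory. The primary list is mostly laboratory hormones, plus ovulation rate and two visual scores (modified Ferriman-Gallwey, Ludwig). Outcome assessors are stated to be blinded.

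**5. Precision of a naive-only analysis.** Section 2.2 gives 60 women per TCM group, 30 per arm, with 20% withdrawal. That leaves 30 × 0.8 = 24 per arm within a TCM group and 2 × 24 = 48 per arm with both groups pooled. The article states no effect size, SD or power, so its sample size cannot be reproduced. At two-sided 0.05 and 80% power the detectable standardised difference is (1.960 + 0.842) × √(2/n):

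| Set analysed | n per arm | Detectable d |
|---|---|---|
| One TCM group, all women | 24 | 0.81 |
| One TCM group, 10% to 40% experienced women removed | 21.6 to 14.4 | 0.85 to 1.04 |
| Pooled, all women | 48 | 0.57 |
| Pooled, 10% to 40% experienced women removed | 43.2 to 28.8 | 0.60 to 0.74 |

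The 10% to 40% range is an assumption. The table shows why the naive-only comparison can be supportive but not decisive.

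**The case against.** The strongest reply is that nothing shows experienced women to be common in this trial. The Introduction does say that side effects of conventional therapy lead women with PCOS towards complementary medicine, and section 2.5 says "Treatments will take place at a research center/private TCM clinic". A reader might infer that the trial draws on TCM users. The documents do not support that. The Introduction is general background, the clinic is a possible place of treatment and not a source of referrals, and section 2.2 recruits through family doctors and hospital gynaecology or endocrinology. This part of the objection stands.

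A reader might also put a size on the blinding bias by multiplying an assumed experienced share by an assumed gap, for example 0.10 × 0.3 = 0.03 SD up to 0.40 × 0.5 = 0.20 SD. Both inputs are invented, and the product credits all guessing to experience although the contrast between arms is open to everyone. Those figures should not be used.

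Three further points stand. Carry-over is balanced in expectation, so it dilutes and does not favour an arm. The self-rated scales are exploratory. A washout still admits women with acupuncture further in the past, who may also recognise the sham. Admitting them is a defensible choice that widens applicability.

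What the objection does not reach is current and recent treatment. The list is stated as the trial's eligibility rule, and under it a woman in the middle of a course of acupuncture is eligible.

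**Conclusion.** The point holds in a limited form. Section 2.4 allows women with current or recent acupuncture to be randomised. The likely effect is dilution of the active-sham contrast, with some added risk to participant blinding that bears mainly on SF-36 and the Zung scales. Neither can be sized from the documents, because they give no share of experienced women, no measure of persistence and no guessing rates. If recent acupuncture is rare among the referrals, the effect is small.

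It would go too far to say that prior exposure cannot be separated afterwards. The article does not itemise its intake record, so the item may be collected. The change is worth making because the rule is stated, the gap is plain and the correction is cheap. It does not call the design as a whole into question.

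**What to change.** 1. Add to 2.4 an exclusion for current acupuncture and for acupuncture within a washout period before screening. The sponsor should fix the length in advance.
2. Record lifetime acupuncture exposure (never or past) at intake, if this is not already done.
3. Name one supportive sensitivity analysis: the active versus sham comparison repeated in acupuncture-naive women. This addresses past users whom the washout still admits.

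The cost is one eligibility line, one intake question and one extra analysis. Referrals are lost in proportion to the share with recent acupuncture, so cost and benefit rise together: if few are excluded, little dilution was at stake. The sensitivity analysis will be less precise than the main one. The first two changes must be in place before enrolment. Section 3.4 still describes registration and ethics approval as future steps, so on the article's account there is time.

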### 2.5. Intervention

A schedule was established for a total of 12 weeks of intervention, with a frequency of treatment of 1 time per week during the first 6 weeks and 2 times per month in the following 6 weeks. Treatments will take place at a research center/private TCM clinic (Figure 2 and Table 2).

#### 2.5.1. Active Acupuncture

Points: Traditional Chinese medicine regards the PCOS condition as a mass development syndrome such as kidney Yang deficiency and phlegm plus dampness and/or blood stasis. So, treatment should address the resolution of dampness in the lower Triple Burner, eliminate stasis promoting blood circulation, thus leading to an improved Penetrating (Chong Mai) and Conception (Ren Mai) vessel communication, reinvigorate kidney Yang, harmonize Qi circulation in the spleen and lung vessels, and dispel possible internal heat as well as lead to a clear Shen. Chosen points for this study protocol are discriminated and justified in Table A1 and Figure 1a–c.

In short, the combination of Gǔangyúan REN-4 with Tàixī KID-3 and Tàichōng LIV-3, both Earth points, contributes to treat kidney deficiency and tonify liver blood, soothing the liver’s Yang hyperactivity, and rooting the Shen, thus, calming emotions [49]. The sedation of Bàihuì DU-20 may add to the relief of anxiety. On the other hand, Zhōngjí REN-3 and Zhōngwăn REN-12 will also contribute to moving the stagnated Qi associated with phlegm-dampness syndrome. Stimulating points in the lower Triple Burner, namely, Shēnmài BL-62 and Si3 Hòuxī SI-3, we expect an improvement of issues related to food, fluids, blood stasis, accumulated phlegm, and stagnant emotions derived from kidney deficiency associated with phlegm-dampness syndrome. The Qi stagnation observed in these patients usually leads to an imbalance in the transforming function of the Earth element for which Tiānshū ST-25 and Sānyīnjiāo SP-6 may help to restore the Qi and Xue circulation for a general improvement of homeostasis [45]. In women presenting blood stasis, the Conception–Governor vessel circulation is prone to an imbalance that leads to frequent amenorrhea and fertility issues. For that, we suggest regulating the Conception vessel to promote a healthy reproductive cycle by opening Ren Mai and restoring harmony by pairing the Luo points Zhàohăi KID-6 with right Lièquè LU-7 and right Nèiguān P-6 with left Gōngsūn SP-4 to regulate the Conception, Governing, and Penetrating vessels [49]. We would also add Tiānshū ST-25, Guīlái ST-29, and Yīlíngqúan SP-9 to stabilize and harmonize the Earth movement, nourishing blood and eliminate stasis with the spleen’s reinforcement [45]. Based on the characteristics of the referred points, we designed two protocols: Protocol A includes: Zhōngjí REN-3 (dispel), Gǔangyúan REN-4 (tonify), Zhōngwăn REN-12 (dispel), and Tiānshū ST-25 bilaterally (dispel) and Sānyīnjiāo SP-6 bilaterally (tonify). Needles will also be placed in extra segmental acupuncture points: Bàihui DU-20 (sedation), Tàichōng LIV-3 (dispel), Tàixī KID-3 (tonify), Shēnmài BL-62 (dispel), and Hòuxī SI-3 (tonify). In total, 14 needles will be placed (Table A1, and Figure 1a). Protocol B: consists of 16 needles placed in segmental abdominal points; Zhōngjí REN-3 (dispel), Gǔangyúan REN-4 (tonify), Qìhăi REN-6 (tonify), Tiānshū ST-25 (dispel), Guīlái ST-29 (dispel), bilaterally, and extra segmental points: Yīlíngqúan SP-9 bilaterally (tonify), Nèiguān P-6, left Gōngsūn SP-4 (tonify), left Zhàohăi KID-6 (tonify), Tàixī KID-3 (tonify bilaterally), right Lièquè LU-7 (tonify), and Bàihuì DU-20 (sedate) (Table A1 and Figure 1b). Needles and insertion: disposable 25 **×** 25 needle will be used. Insertion depth will be 15–35 mm into skeletal muscle or fibrous tissue. The depth of needle insertion could vary according to the location depth of the acupoint between patients depending on body mass index (BMI), as depth should be enough to reach muscle/fibrous tissue. Stimulation: When needles are inserted, they will be stimulated by manual rotation circa 180 degrees back and forth to evoke tingling sensation—so called de Qi—reflecting activation of sensory afferents. As soon as Qi sensation is reached, the needle should not hurt or cause any pain or discomfort. After 10 min, needles will be stimulated manually. This should be repeated after 20 min and again after 30 min. Two sets of acupuncture points will be used according to the symptoms of each study group.
